### Secondary objectives

Secondary objectives include determining whether the use of INJ-BUP is associated with better outcomes than SL-BUP/NLX in: opioid craving; use of other illicit substances and alcohol; preventing opioid overdose; reducing mental health symptoms (including depression, PTSD, and suicidality; homelessness); incarceration and criminal legal involvement; self-reported risky sexual and injection drug use behaviors and the incidence of new cases of HIV, HBV, and HCV. In addition, the total cost impact of INJ-BUP and cost-effectiveness from the perspective of VHA and of society will be evaluated. We will thus also assess non-VA service utilization, especially since the MISSION ACT [38], allows a Veteran to receive care from a community provider paid for by the VA. Table 2 summarizes the Schedule of Assessments including self-report and biological measures and their administration times. Data will also be captured to identify reasons for missed study injections as well as overall study visits.

## Special circumstances

The following circumstances are anticipated for this population and considerations were made regarding study participation, procedures, and follow-up related to each.

### Incarceration

Participants cannot be interviewed, have study procedures administered or receive study drug while incarcerated. However, if an incarceration episode has been concluded when discovered, and no immediate future risk of incarceration is present, then continuation of participation is reasonable. The study team may review the medical records of participants who are incarcerated. Participants with ‘brief’ incarceration periods, defined as a period of less than the remainder of the participant’s 52-week study period, may be eligible to continue study participation if they so choose after they are released back to the community.

### Non-fatal and fatal accidental overdose

Information regarding accidental drug poisoning (i.e., overdose) will be obtained and tracked via participant self-report, naloxone distribution records, hospital records both within and outside VHA, as well as CDC accidental drug poisoning data, if possible. If a participant experiences non-fatal accidental drug poisoning, this would not necessarily impact eligibility.

### Newly diagnosed HIV/HBV/HCV infections

Information regarding HIV/HBV/HCV will be obtained and tracked via participant self-report, HIV/HBV/HCV blood tests at periodic study visits (see Table 2), and hospital records both within and outside VHA. If a participant has a newly diagnosed HIV/HBV/HCV infection, this would not necessarily impact eligibility or continued study participation.

### Pregnancy

Urine pregnancy testing will be conducted on all Veterans of childbearing potential at screening, induction, baseline, and randomization as well as all follow-up visits during which study medication is prescribed/administered as denoted in Table 2. For these female Veterans, pregnancy, breastfeeding, and/or failure to practice an effective method of birth control for the duration of participation in the study are exclusion criteria (Table 1). In the event of a positive pregnancy test, the participant will be referred to clinical care and study-related treatment will stop.

## SARS COV2 (COVID-19)

As the clinical research landscape is ever-changing during the coronavirus disease (COVID-19) pandemic, researchers must adapt in making decisions about implementing the research protocol in clinical trials. Regulations governing buprenorphine treatment were relaxed in response to the COVID pandemic to allow initiation and maintenance of buprenorphine by telemedicine without in person visits. However, due to the needs of the research to collect urine in person and the relatively low likelihood of patients presenting with active COVID infection, some in person visits were deemed necessary.

Study procedures were modified to be conducted in a manner that protects both staff and participants from COVID-19 by minimizing any risk for inadvertent transmission and by limiting exposure time. All study drug initiations, provisions of SL-BUP/NLX prescriptions, and injections of INJ-BUP are performed in person.

If potential participants are COVID-19 positive or in COVID-19 isolation, they may be given information about the study via telephone/telehealth, but may not be consented, as these procedures must occur in-person to assess and ensure informed consent. However, eligibility may be reconsidered when the patient has clinically improved.

Enrolled participants are screened per standard of care at each participating site for COVID-19 symptoms and exposure; research procedures may continue on a full face-to-face or limited face-to-face basis for those who screen negative. If an already enrolled participant is under quarantine or isolation orders, they may not be seen in person for study-related procedures. Study procedures may be rescheduled and/or conducted via telephone/telehealth. Study visit assessments and procedures that may be conducted via telehealth/telephone have been identified and include predominantly self-report measures. In order to capture information about COVID-19 and its effect on drug use, a COVID-19 questionnaire has been added to the protocol for administration at baseline and every 3 months.

## Analytic plan

The primary objective is to determine if long-acting injectable formulation of buprenorphine is superior to the sublingual formulation. There are two complementary primary endpoints: retention on study assigned MOUD and opioid abstinence. For the retention outcome, a time-to-event analysis using a two-sided log-rank test will compare the treatments. For the abstinence outcome, the mean number of opioid free UTOX screens in conjunction with self-reported abstinence at 28 distinct time points in each treatment arm will be compared by a Student t-test. Both measures must be negative for classification as abstinent. We will accrue over the follow-up period the total count of such self-report consistent opioid free urine tests. In secondary analyses UTOX samples obtained during study visits will be compared to self-reports of opioid use. All secondary analyses are exploratory and therefore not powered. All analyses of these outcome variables will be done with a single predictor, formulation (simple or one variable), or with formulation and a stock of covariates (multivariable) that predict the outcome. Predictive variable will be used for secondary analyses in which the outcomes used in the primary analyses will be assessed based upon explanatory variables that might affect treatment group outcomes between the two intervention groups.

All clinical data and study documents will be monitored by the CSP Coordinating Center (CSPCC) using an electronic data capture and clinical trial management system and follow existing regulations and standard operating procedures in handling study and participant information and used in VA Cooperative Studies.

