The exclusion criteria are also minimal to enhance generalizability, while maximizing patient safety. These include conditions (e.g., psychiatric conditions) requiring a higher level of care or medical conditions that preclude the use of buprenorphine. While participants are expected to have comorbid substance use disorders, whether to exclude participants using sedative hypnotics was carefully considered. Recent guidance from the American Society of Addiction Medicine (ASAM) [32] encourages treatment with buprenorphine even in those using sedative hypnotics since buprenorphine protects against risk of overdose from opioids. In this study, those participants at highest risk of combining medications, defined as those with a DSM-5 diagnosis of current sedative hypnotic use disorder are excluded.

Similarly, it is expected that participants will have medical comorbidities including hepatitis B and C and HIV. Only those participants for whom buprenorphine is medically contraindicated or who require intensive medical management (e.g., Childs-Pugh Class C cirrhosis) are excluded. Those with pending felony charges are also excluded due to likelihood of incarceration interfering with participation. In addition, in response to the COVID-19 pandemic, exclusion criteria exclude those with current moderate to severe COVID-19 symptoms who were at risk of intubation or critical illness. Those participants are able to join if they meet eligibility criteria after they recover from the acute phase of the infection.

Twenty geographically diverse sites were chosen across the United States with consideration for sites with facilities capable of supporting CSP research as well as those areas hard-hit by the opioid epidemic as shown in Fig. 2.

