### Sample size and power analysis

The sample size estimates primarily arise from the assumption of an overall at least 40% retention after 52 weeks. The study treatment retention times will be compared using a log-rank test, assuming that for the alternative hypothesis, the hazard ratio (injected over sublingual) is 0.74 or smaller. The two-sided hypothesis also rejects the null hypothesis if the hazard ratio is 1.36 or larger. For the comparison of abstinence, using the t-test, the alternative hypothesis posits a difference in proportions of 10% (a difference of 1.5 if mean counts are about 15). Under these assumptions, with a total size of 952 participants, this study has overall 90% power to reject both null hypotheses. Each test assumes a Type I error of 2.4% (where the interim uses 0.1%). This assumes no participants drop out (they are treatment failures), but that follow-up time ends when the participant dies or has a long-term hospitalization, is institutionalized, or incarcerated.

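### The primary retention test is described as a plain log-rank across 20 sites; stratifying it by site would be a cheap, optional gain in power

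*Protocol article*

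**What the plan says.** The Analytic plan states that for the retention outcome "a time-to-event analysis using a two-sided log-rank test will compare the treatments". It adds that "All analyses of these outcome variables will be done with a single predictor, formulation", or with formulation plus a set of covariates, and then gives the covariates their place: "Predictive variable will be used for secondary analyses".

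The section Sample size and power analysis repeats the choice: "The study treatment retention times will be compared using a log-rank test". The alternative is that "the hazard ratio (injected over sublingual) is 0.74 or smaller", each co-primary test has a type I error of 2.4%, and overall retention at 52 weeks is assumed to be at least 40%. The claim is 90% power to reject both null hypotheses with 952 participants.

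On sites, the section Study population says: "Twenty geographically diverse sites were chosen across the United States". The section Devising clinically relevant treatment arms gives 1:1 central allocation but does not say whether site is a stratum.

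**The concern.** The natural reading is that the primary retention comparison uses formulation alone and that all adjustment is secondary. Sites differ in region, and site investigators, though mostly psychiatrists, include primary care physicians (Study dose). If the baseline rate of discontinuation varies by site, two things follow. Pooling the sites pulls the marginal hazard ratio towards 1, which lowers power. And if allocation is balanced within site, the plain test's variance ignores that balance, so the test rejects less often than its nominal level.

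At stake are some points of power on one of two co-primary endpoints, in a design with little slack on that endpoint. The trial already records the variable that would recover them.

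**Working it through.** **1. The plan's own figure.** Inputs from Sample size and power analysis: N = 952, overall retention 40%, HR 0.74, two-sided alpha 2.4%.

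- Events: 952 × 0.60 = 571.
- Schoenfeld power: Φ(½ × √571 × |ln 0.74| − z(0.988)) = Φ(11.948 × 0.3011 − 2.257) = Φ(1.34) = 91.0%. Freedman's form gives 90.5%.

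The retention part reproduces. The joint 90% then needs t-test power of about 0.90/0.91 = 99% if the two tests are taken as independent. The SD that this requires is not in the article. Retention therefore has about 1 point of slack over 90%.

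**2. The two tests.** With U_k the observed minus expected events and V_k the variance in site k, the stratified statistic is ΣU_k / √ΣV_k. The plain test computes one U and one V over all participants.

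**3. What an assumed site SD means.** With 40% retention at a typical site, the cumulative hazard is −ln 0.40 = 0.916. A site 1 SD away retains exp(−0.916 × e^(±SD)):

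- SD 0.2: about 33% to 47%
- SD 0.3: about 29% to 51%
- SD 0.5: about 22% to 57%

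The article gives no between-site figure. Its Background cites 12-month retention of 61.6% and 35% in two Veteran cohorts, a log-hazard difference of ln(1.050/0.485) = 0.77. Those cohorts differ in period and perhaps in definition, so they do not estimate the site SD. They show only that SDs of 0.3 to 0.5 are not extreme.

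**4. Power by simulation, HR 0.74 within every site.** 20 sites, normal site effects on the log hazard. Sets A to C have 3,000 trials per setting, exponential times, overall retention held at 40% and a Monte Carlo SE of about 0.5 to 0.7 points. Sets D and E have 6,000 trials per setting and 13 four-week event times. Entries are plain / stratified power in %.

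| Set | SD 0 | SD 0.2 | SD 0.3 | SD 0.5 |
|---|---|---|---|---|
| A: balanced within site, equal sites | 91.1 / 91.0 | 89.5 / 89.7 | 89.1 / 90.6 | 85.8 / 90.5 |
| B: balanced within site, unequal sites | 90.7 / 90.1 | 89.4 / 89.7 | 88.8 / 90.1 | 85.7 / 89.7 |
| C: not balanced by site | 91.3 / 90.5 | 89.1 / 89.4 | 89.1 / 90.2 | 84.3 / 89.1 |
| D: balanced within site | 90.3 / 90.1 | not run | 89.7 / 90.6 | 85.3 / 89.6 |
| E: not balanced by site | 90.6 / 89.9 | not run | 88.7 / 90.0 | 84.0 / 89.2 |

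**5. Level under the null (nominal 2.4%).** With allocation balanced within site, the plain test rejects 2.1% at SD 0.3 and 1.7% at SD 0.5; the stratified test rejects 2.4% at both. Without site balance, the plain test shows no such conservatism (2.7% and 2.9%, against a Monte Carlo SE of √(0.024 × 0.976/3000) = 0.28 points).

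**6. If 0.74 is the pooled hazard ratio.** At SD 0.5, a within-site HR of 0.74 corresponds to a pooled HR of about 0.76. As a check, Φ(11.948 × |ln 0.76| − 2.257) = Φ(1.02) = 85%, close to the plain test in the table. Setting the within-site HR to 0.717 brings the pooled HR to about 0.74. The plain test then keeps 91% to 92% power at SD 0.5 (2,500 trials per setting), and stratifying adds about 2.5 to 3 points above that.

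**The case against.** The strongest reply is that the article never calls the test unstratified. A site-stratified log-rank still has formulation as its only predictor, so the single-predictor sentence does not exclude strata. Test strata are also the kind of detail a condensed article leaves to the full protocol or SAP, neither of which is shown. This stands as a limit: the point applies to the test as the article describes it, and falls away if the full documents already stratify. A reader might infer that the plan has ruled out stratification; the text does not go that far.

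Second, a plain log-rank is a valid test, holds its level or is conservative, and matches the test used to size the trial. That stands too.

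Third, site differences are not shown. All sites are in one health system, with the same film, 28-day schedule, visits and counselling, and all investigators treat opioid use disorder. At SD 0.2 the gain is negligible.

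Fourth, a reader might infer that true power is about 85% rather than the planned figure. The documents do not support that. It needs an SD of 0.5, for which they give no figure, and it needs 0.74 to be a within-site effect. The sample size section attaches 0.74 to a log-rank on retention times with overall retention of 40%, which can equally be read as pooled. It also says 0.74 or smaller.

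What survives is the asymmetry: a small possible cost against a possible gain of several points, on either reading of the hazard ratio.

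**Conclusion.** The point holds as a suggestion for a more efficient primary test; nothing in the plan is wrong here. The direction is secure: stratifying loses at most about 1 point when sites are alike and gains when they are not. The size is not secure, because it follows the assumed site SD: about 0 points at 0.2, 1 to 2 at 0.3 and 4 to 5 at 0.5 under a within-site HR of 0.74, or about 2.5 to 3 at 0.5 under a pooled one. A fall below planned power occurs only on the within-site reading. The conservatism under the null arises only if allocation is balanced within site, which the article does not state. The figures also assume a hazard ratio common to all sites and no censoring other than at 52 weeks.

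**What to change.** Unless the full protocol or SAP already does so, make the primary retention test a two-sided log-rank stratified by site and by any other randomization strata. Take the hazard ratio from a Cox model stratified in the same way. Pool very small sites by a rule fixed before results are unblinded. Keep the unstratified log-rank as a sensitivity analysis. If the full documents already stratify, a line confirming it is enough.

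The cost is a sentence or two in the analysis plan, with no change to sample size, data collection or conduct. The downsides are about 1 point of power or less if sites do not differ, and a reported hazard ratio that becomes a within-site one, which should be said where it is presented.

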Once reaching the target dose, eligible participants are randomized 1:1 to receive either continued daily SL-BUP/NLX at the dose identified in the induction period or to receive monthly subcutaneous abdominal INJ-BUP with a target dose of 300 mg, with the option to use 100 mg dose. Randomization is performed centrally by the CSP Clinical Research Pharmacy Coordinating Center (CSPCC) using an interactive web-based randomization program that allows for randomization of participants in real time by authorized study team members at each site who submit a randomization request form. The study participant is allocated to the appropriate treatment arm according to the randomization schema and a certificate is generated. The certificate is used by the local site investigator and research pharmacist to direct study drug dispensing. Participants are informed of their randomized treatment assignment during their visit, and prior to initiation of either SL-BUP/NLX or INJ-BUP.

This is an open label comparative effectiveness study so neither staff nor participants are blinded to treatment assignment.

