Self-reported drug use is collected using the TLFB calendar method, in which study personnel record the participants’ reported opioid use for each day since the last study visit. The TLFB is reliable and valid when used by trained interviewers and when there is no penalty for reporting use of drugs. The advantage to this method is that data are collected retrospectively to the last visit, so a missed appointment does not necessarily result in missing self-report data; limitations include reliance on self-report and lack of objective measurement. For that reason, a biological measure, with UTOX as standard, is also collected as an indicator of opioid abstinence. UTOX for this study is a UTOX-13 panel from a centralized lab, Redwood Toxicology, and collected at each study visit as indicated in Fig. 3 and the Schedule of Assessments in Table 2 and measures opioid drug use including oxycodone/noroxycodone, benzodiazepines, ethyl glucuronide, methadone, fentanyl, buprenorphine, tramadol, methylene-dioxy-methamphetamine (MDMA), amphetamines, cocaine metabolite, opiates, cannabinoids, and THC/creatinine ratio. UTOX screening is a routine part of buprenorphine maintenance treatment. UTOX screening methods have the issue of how to handle missing data [37]. For this trial, the conservative method that assumes missing UTOX is indicative of use is used (although participants may miss appointments for other reasons) and is consistent with most published research. Both the TLFB and UTOX data must be negative for opioid use to deem a participant abstinent.

**Table 2 Tab2:** CSP#2014, VA–BRAVE study assessments

Assessment	Screening	Baseline	Randomization	Weeks 1–3	Medication-research visits	Non-medication visits	End of study visit (week 52)
Biological assessments							
Urine pregnancy test	√	√	√		√		√
Physical exam	√				Week 24		√
Liver and kidney function, complete blood count (CBC)	√				Weeks 4, 12, 24		√
Electrocardiogram (EKG)	√				Week 24*		
Urine toxicology test		√		√	√	√	√
Blood HIV, hepatitis B (HBV), and hepatitis C (HCV)		√			Week 24		√
Blood buprenorphine and norbuprenorphine		√			Week 24		√
Interviewer administered assessments							
The MINI International Neuropsychic Interview (MINI) [39]	√	√					√
Clinical Opiate Withdrawal Scale (COWS) [40]		*	√	*	*	*	*
Clinical Institute Withdrawal Scale (CIWA-Ar) [41]	√	*	*	*	*	*	*
Patient Health Questionnaire-9 (PHQ-9, item 9 only) [42]	√			√	√	√	√
Timeline follow-back [43]		√		√	√	√	√

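### The primary abstinence comparison is a valid but unadjusted t-test, although baseline opioid use is collected; adjusting for it would add precision of uncertain size at little cost

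*Protocol article*

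**What the plan says.** The Analytic plan section builds the abstinence endpoint as a sum over 28 time points: "We will accrue over the follow-up period the total count of such self-report consistent opioid free urine tests". The arm means of that count "in each treatment arm will be compared by a Student t-test", with no covariate. The sample size section uses the same t-test.

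The Analytic plan also allows models containing formulation plus covariates that predict the outcome, but gives them a different role: "Predictive variable will be used for secondary analyses" of the primary outcomes. It calls all secondary analyses exploratory and unpowered.

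Table 2 (Outcomes section) ticks timeline follow-back and the urine toxicology test in the Baseline column, which stands before the Randomization column.

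**The concern.** Opioid use before randomization is a natural candidate predictor of later opioid-free visits. The trial measures it by the same two instruments that make up the endpoint, but the confirmatory test does not use it. Adjusting for a prognostic baseline variable in a randomized trial narrows the confidence interval and corrects for chance imbalance in that variable. With a linear model, the quantity estimated is still the difference in mean counts. The exploratory multivariable models cannot supply this benefit, because they do not carry the confirmatory claim.

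What is at stake is precision on one of two co-primary endpoints. Bias and false-positive error are not at issue.

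**Working it through.** **Inputs from the article.** N = 952, and "eligible participants are randomized 1:1 to receive either continued daily SL-BUP/NLX" or the injection, so 476 per arm. Final alpha is 0.024 per test (0.001 at the interim). Two-sided testing is stated for retention ("a time-to-event analysis using a two-sided log-rank test will compare the treatments") and assumed here for the t-test, giving z = 2.257. The abstinence effect is described as 10%, glossed as 1.5 counts on a mean near 15. Ten percentage points of 28 visits would be 2.8 counts. Retention: hazard ratio 0.74 and 40% retained overall.

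**Not in the article, so assumed.** The SD of the count, and the correlation r between baseline use and the count.

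**Step 1: the plan's own figure.** The claim is that "with a total size of 952 participants, this study has overall 90% power to reject both null hypotheses".
- Retention events: 952 × 0.60 = 571.
- Retention power (Schoenfeld): Φ(0.3011 × √571.2 / 2 − 2.257) = Φ(1.341) = 91.0%. This agrees with 90% for retention.
- Joint power cannot be reproduced without the SD. If the two tests are independent, abstinence needs 0.900 / 0.910 = 98.9% power.
- Since √(2/476) = 0.06482, the implied SD is 1.5 / [0.06482 × (2.257 + 2.289)] = 5.09 for a 1.5-count difference, or 9.50 for 2.8 counts.

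**Step 2: effect of adjustment.** Residual SD = SD × √(1 − r²). Power = Φ(δ / (residual SD × 0.06482) − 2.257). The variance falls by r²: 1%, 4%, 9%, 16% and 25% at r = 0.1, 0.2, 0.3, 0.4 and 0.5.

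| δ | SD | r = 0 | 0.1 | 0.2 | 0.3 | 0.4 | 0.5 |
|---|---|---|---|---|---|---|---|
| 1.5 | 5.09 (implied, independence) | 98.9% | 99.0% | 99.1% | 99.4% | 99.7% | 99.9% |
| 1.5 | 6.54 (abstinence test alone at 90%) | 90.0% | 90.3% | 91.2% | 92.7% | 94.6% | 96.6% |
| 1.5 | 8.4 (assumed) | 69.1% | 69.6% | 71.0% | 73.6% | 77.3% | 82.2% |
| 1.5 | 10 (assumed) | 52.3% | 52.7% | 54.2% | 56.7% | 60.6% | 66.1% |
| 2.8 | 8.4 (assumed) | 99.8% | 99.8% | 99.9% | 99.9% | >99.9% | >99.9% |
| 2.8 | 10 (assumed) | 98.0% | 98.1% | 98.4% | 98.8% | 99.3% | 99.7% |

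For orientation, a count spread evenly over 0 to 28 has SD √((29² − 1)/12) = 8.4.

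**Step 3: joint power.** With SD 5.09 and independence, joint power goes from 90.0% to 90.1%, 90.5% and 90.9% at r = 0.1, 0.3 and 0.5. It can never exceed the 91.0% of the retention test, whatever is done for abstinence.

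**Step 4: the price if r is zero.** With k covariates the variance grows by about k/(949 − k). Two covariates cost 2/947 = 0.2%. Adding 19 indicators for the 20 sites costs 21/928 = 2.3%.

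**The case against.** The strongest reply is that nothing here is wrong. A t-test on a mean count with 476 per arm is valid, and the sample size rests on the same test. Adjusted analyses of the same outcome are already planned as secondary. All of that stands. A reader might infer from the heading that the primary test is faulty; the article gives no support for that.

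A reader might also infer that the trial is underpowered for abstinence and that adjustment would rescue it. That depends on SDs such as 8.4 or 10, which appear nowhere in the article, and on reading the effect as 1.5 counts. Taken at face value, the stated 90% joint power implies a smaller SD, and retention is then the limiting test. Conversely, the article does not establish an SD near 5. With 40% retained and missing urine counted as use, a wider spread is possible. Neither end can be settled from the text.

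The correlation may also be weak. Every entrant must have used opioids recently, some are already on treatment for under 30 days, and attendance drives part of the count. At r = 0.1 the gain is half a point of power or less in every row of the table.

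A third inference would be that leaving the covariates unnamed means they will be chosen from the data. An article commonly leaves that list to the full protocol or analysis plan, so this is not a finding.

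Finally, the trial is open label with an interim look, so there is no unblinding date to protect a late change. This stands and governs the timing of the fix. None of these points removes the improvement, because the role of covariates in the confirmatory test is something the article itself fixes.

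**Conclusion.** The point holds as an efficiency improvement of uncertain size. The confirmatory abstinence test sets aside baseline information that the trial already collects. A prespecified linear adjustment would keep the mean-difference estimand and, at about 476 per arm, the type I error.

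The variance reduction is r squared, with r assumed. What that buys ranges from about 2 to 13 points of abstinence power (1.5 counts, SD 8.4, r 0.2–0.5) down to at most about 1 point (1.5 counts, SD 5.1). There is little to gain if 2.8 counts was intended. These figures use normal approximations, two-sided testing and a common r in both arms; the SD of 5.1 also assumes that the two co-primary tests are independent.

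**What to change.** Before the interim look and before any between-arm comparison of outcomes, name as the primary abstinence analysis a linear regression of the opioid-free count on arm, baseline days of opioid use (timeline follow-back) and baseline urine result, with robust standard errors. Site may be added. State the fixed covariate list, the form of each covariate, the look-back window for days of use, and a simple rule for missing baseline values that does not depend on arm. Report the adjusted mean difference with its interval and keep the Student t-test as supportive. State the SD and the correlation assumed, so that the expected gain can be judged. If the arms have already been compared on outcome, leave the t-test as primary and report the adjusted model as supportive.

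The cost is a short amendment to the analysis text, a few degrees of freedom, and a slight departure from the test behind the sample size. No new data are needed.
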